**3.4 Calculation of sample size**

Our calculations of sample size and power are based on the primary outcomes, utilizing a two-sided analysis with a statistical power of 90 % (1 – β = 0.90) and a significance level of α = 0.05. Owing to the lack of prior studies examining cardiovascular ultrasound therapy following PCI, the sample size was determined following an extensive evaluation by a panel of experts. Targeting long-term inflammation and cardiovascular efficacy, they selected high-sensitivity C-reactive protein (hsCRP) as the primary biomarker, given its relevance and the larger sample size required by interleukin 6.

Cardiovascular ultrasound is estimated to reduce hsCRP levels by an average of 4 mg/L. To meet this target, 160 participants (80 per group in a 1:1 allocation) are projected to be needed. Factoring in an anticipated dropout rate of 20 %, the final sample size would be adjusted to 200 participants (100 per group), ensuring adequate statistical power and robustness for the study’s objectives.

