**3.5 Randomization and blinding**

Using a randomized 1:1 ratio, participants will be allocated into either of two groups: the cardiovascular ultrasound therapy group and the control group. This process will be facilitated by a computer-generated randomization sequence. To uphold the integrity of the allocation process, a team of research assistants not involved in clinical care or outcome assessment will meticulously craft sequentially numbered, opaque, sealed envelopes based on the predefined randomization list. This meticulous approach will ensure the safeguarding of confidentiality and the autonomy of allocation data. When appropriate, the assistants will open envelopes and ensure the coordination of therapeutic interventions.

Given the distinctive visual and operational characteristics of cardiovascular ultrasound therapy, the assignment results will not be concealed from the attending physicians or the patients. Only the investigative team members responsible for the collection of primary outcome data will remain masked. Consequently, the study design adheres to the framework of a nonblinded controlled trial. Patients will retain the prerogative to decline study participation, in which case they would receive standard care only.

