**3.7.2 Intervention description**

Participants allocated to the intervention group will undergo a 10-day regimen utilizing a medical cardiovascular ultrasound therapy device (838C-M-L-I/II, Shenzhen, China). The ultrasound instrument is equipped with a sound head comprising five transducer units operating at an ultrasonic frequency of 0.84 MHz with a sound intensity range of 1 W/cm^2^–1.25 W/cm^2^. The therapeutic ultrasound sessions require a controlled environmental temperature. Patients will assume the supine position, exposing the precordial region, with the 5-pronged head positioned parallel to the heart’s long axis; it should cover the entire precordial region including the right and left coronary arterial trunks and the aortic root (Fig.1). The five transducer units function sequentially in a scanning pattern, with each unit operating for 5 seconds and transitioning with a 0.5-second interval, following a clockwise rotation until the treatment has been completed. The cardiovascular ultrasound therapy device operates in a pulsed mode, and each treatment session lasts for 20 minutes; there would be two daily sessions for a total of 20 treatments. The control group was not given extracorporeal cardiac ultrasound therapy. Participants in the control group will not receive cardiovascular ultrasound therapy. cardiovascular ultrasound therapy will be assessed at baseline (24th-hour post-PCI), on the 10th day, and at the end of the first and third months post-intervention. If it is necessary to change the medication regimen as much as possible, if it is necessary to change the medication regimen, it should be decided after evaluation by the investigator, and if the medication regimen that does need to be changed has an impact on the test results, the patient should be excluded and the reasons for changing the medication regimen should be recorded in detail.

[figure not shown]

Fig. 1. Diagram of ultrasound head placement.

A: Patients undergoing cardiovascular ultrasound therapy. B is used in patients with occlusion of one coronary artery and C is used in patients with occlusion of both coronary arteries.

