**4** **Statistical analysis**

The baseline characteristics of both groups will be summarized using appropriate descriptive statistics. Analysis of both primary and secondary outcomes will be based on the intention-to-treat approach, ensuring that all participants remain assigned to their original group throughout the study.

Normally distributed data will be presented as the mean (standard deviation), and non–normally distributed data will be depicted as the median (interquartile range). Group comparisons will be conducted using independent sample tests, and within-group comparisons before and after treatment will be evaluated using paired sample tests. Clinical symptom variables will be portrayed as percentages. Categorical data will be assessed using either the chi-squared test or Fisher’s exact test. A significance level of.05 will be employed to interpret the P values. The statistical analysis will be conducted utilizing SPSS version 26 statistical software (IBM, Armonk, NY).

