**4.3 Analytic methods for handling protocol nonadherence and statistical methods for handling missing data**

We anticipate minimal missing data (<10%) for the primary outcome given that all participants will be in patients with regular daily contact maintained during treatment. The evaluation of missing data effects will involve comparing differences under plausible and extreme missing data scenarios. In the event of a significant primary test result, we will also assess the interaction size between group assignment and missing data necessary to render the difference nonsignificant. Should 10% or more of the baseline samples be excluded due to missing data, we will apply multiple imputation techniques for comprehensive analysis.

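### Section 3.5 masks only the collectors of primary outcome data, while section 3.7.2 allows result-linked exclusion of randomised patients by staff who can see the arm, against the intention-to-treat commitment in section 4

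*Protocol*

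**What the plan says.** Protocol section 3.5 (Randomization and blinding) first states that "the assignment results will not be concealed from the attending physicians or the patients". It then limits masking to one group: "Only the investigative team members responsible for the collection of primary outcome data will remain masked". It concludes: "Consequently, the study design adheres to the framework of a nonblinded controlled trial". No other section masks those who settle the analysis set or provides for a masked review of exclusions.

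Section 3.7.2 (Intervention description) deals with medication changes during the trial. The investigator evaluates whether a change is needed, and then "if the medication regimen that does need to be changed has an impact on the test results, the patient should be excluded", with the reasons recorded. Nobody else is named as deciding the exclusion. Section 3.2.2 also lists changes to lipid-lowering, antiplatelet and antihypertensive regimens during treatment as an exclusion criterion, although this can be known only after treatment has started.

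Section 4 (Statistical analysis) commits both primary and secondary outcomes to intention-to-treat, with participants kept in their assigned group.

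The primary outcomes (section 3.9.1) are serum hsCRP and interleukin-6 on day 10. The design error rate comes from section 3.4: "utilizing a two-sided analysis with a statistical power of 90 % (1 – β = 0.90) and a significance level of α = 0.05".

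**The concern.** The masking is placed where it protects least. Both primary outcomes are blood assays, and whoever collects them has little scope to shift the value. Deciding which patients' values count takes more judgement, and the protocol gives that judgement to staff outside the masked group. It also ties the judgement to the effect on the results.

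An exclusion made after randomisation, with knowledge of arm and with reference to results, can bias the group difference in either direction. Neither randomisation nor masked sample collection corrects that. Because section 4 promises intention-to-treat, a reader of the final report would not expect such removals. If any occurred, a positive hsCRP or interleukin-6 result would be hard to defend against the charge that removals favoured the device. The protocol has no data monitoring committee (7.2), steering committee (7.1) or audit (7.3) that would supply an independent check.

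**Working it through.** **1. Inputs from the Protocol.** Two-sided alpha 0.05, power 90%, 160 evaluable patients (80 per group), 20% dropout, 200 randomised (all section 3.4). For the effect: "Cardiovascular ultrasound is estimated to reduce hsCRP levels by an average of 4 mg/L". No SD is given.

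**2. The plan's own figures.** The dropout step reproduces: 160 / (1 − 0.20) = 200. The 80 per group cannot be reproduced without an SD. Solving for it, SD = 4 / [(1.960 + 1.282) × √(2/80)] = 4 / 0.5125 ≈ 7.8 mg/L. Other SDs would need 33 per group (SD 5), 65 (SD 7), 85 (SD 8) or 132 (SD 10). The check below does not depend on this SD, because under no effect the error rate of a t-test on normal data does not depend on the scale. A log t-test on lognormal hsCRP is the same calculation.

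**3. What masking the text provides.**

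| Decision | Who decides | Masked? |
|---|---|---|
| Collecting primary outcome data | Designated team members (3.5) | Yes |
| Evaluating a medication change and its effect on results, leading to exclusion | Investigator (3.7.2) | No provision |
| Settling the final analysis set | Not stated | No provision |

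**4. Arm-aware removal under no effect.** 20,000 simulated trials, normal data (equivalently, log values), one two-sample t-test fixed in advance. The k highest ultrasound-arm values are removed.

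| k removed | Two-sided error, 80 per arm | Error favouring ultrasound, 80 per arm | Two-sided error, 100 per arm |
|---|---|---|---|
| 0 | 5.0% | 2.4% | 5.0% |
| 2 | 7.2% | 6.0% | 6.9% |
| 3 | 9.3% | 8.4% | 8.4% |
| 5 | 14.5% | 14.1% | 12.9% |

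**5. Hand check for k = 5 at 80 per arm.** Removing the top 5/80 = 6.25% of a standard normal cuts at 1.534.
- Shift in mean: 0.1230 / 0.9375 = 0.131 SD downward.
- Variance of the trimmed arm: 1 − 1.534 × 0.131 − 0.131² ≈ 0.78.
- Pooled SD: √[(74 × 0.78 + 79 × 1) / 153] ≈ 0.946.
- Standard error: 0.946 × √(1/75 + 1/80) ≈ 0.152.
- The test statistic is therefore centred near 0.131 / 0.152 ≈ 0.86 instead of 0. The chance of passing the critical value of about 1.98 in ultrasound's favour is about P(Z > 1.11) ≈ 13%, close to the simulated 14.1%.

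**6. Removal without sight of arm.** Removing five patients from one arm independently of outcome gives 5.0% at 80 per arm and 4.9% at 100 per arm. Removing the same numbers of high values from the pooled data, without arm labels, also stays near 5%.

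**7. Is k = 5 large for this trial?** Five of 80 is 6.25%. That is below the 10% missing-data level that section 4.3 expects the primary outcome not to reach, and below the 20% dropout allowance in section 3.4.

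**The case against.** The best case against the point has four parts.

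*The masking sentence describes trial conduct.* It follows a sentence on physicians and patients and may not have been meant to cover analysts. An SAP, not shown here, could mask the statistician. This is fair, and the absence of a named masked statistician is not itself the finding. But the exclusion in section 3.7.2 is written into the protocol and placed with the investigator, so masking the statistician later would not close it.

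*The exclusion clause may mean a pharmacological effect judged in advance, not observed values.* That reading is possible. The wording does not say so, and it sets no rule on when or by whom the judgement is made.

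*The real problem is the conflict with intention-to-treat.* That conflict is half of the point. Masking alone would not repair it: a masked person would still be removing randomised patients. Both corrections are needed.

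*The error rates assume behaviour that nobody has shown.* Correct. They are worst cases.

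A reader might also infer two further routes, which the documents do not support. The first is free choice among tests. Section 4 says "Group comparisons will be conducted using independent sample tests" and distinguishes normal from non-normal data, but the exact test is commonly left to an SAP. Moreover, the smallest two-sided P over several tests is the same when arm labels are swapped, so any inflation from that source does not measure the masking gap. The second is the missing-data plan. Section 4.3 states: "The evaluation of missing data effects will involve comparing differences under plausible and extreme missing data scenarios". These are sensitivity analyses, accompanied by an assessment of what would overturn a significant result, and they do not determine the primary P value.

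**Conclusion.** The point holds in a limited form. As written, the protocol permits exclusions from the primary comparison that are linked to results and made with knowledge of arm, and it contradicts its own intention-to-treat commitment. In the worst case examined, the two-sided error rises from 5% to about 7%, 9% or 14% when 2, 3 or 5 of 80 ultrasound-arm values are removed, with nearly all of the excess favouring ultrasound.

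This rests on three assumptions: no true effect, normal data on the analysis scale with one fixed test, and removal always of the highest values in one arm. The number of medication changes that would lead to exclusion is not given in the Protocol, so k is an assumption.

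A reader might conclude that the trial's error rate is inflated. The documents show only that it is not protected on this route. A reader might equally conclude that coding the arms A and B would suffice. It would not: coded arms still show which values belong together, so high values can be removed from whichever arm is lower, and a two-sided P does not depend on the labels.

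**What to change.** 1. Amend section 3.5: any decision to remove a patient or a value from the primary analysis of hsCRP or interleukin-6 is made on pooled data without arm labels, and is recorded and dated before unmasking. A/B coding alone is not enough. Fields that reveal the arm, such as treatment-session records and device-related local reactions, are left out of the file used for these decisions.
2. State that the test and the scale of analysis are fixed before any between-arm comparison is run. The detail may sit in the SAP.
3. Reconcile the exclusion in section 3.7.2 with the intention-to-treat statement in section 4, so that the two say the same thing about whether such patients stay in the primary analysis. If intention-to-treat stands, the analysis without these patients can be reported as supplementary.

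These changes concern only which data enter the analysis; nothing is proposed about medication or continuation of treatment. The cost is a recoded data file and a dated decision record. No patients or visits are added, and physicians and patients can remain unmasked.

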**3.6 Informed consent**

The research assistants (CHs) will take informed consent before trial baseline evaluation in the participants’ reception room. Participants will be told why the study is being conducted, what they will be doing, and the possible benefits and risks. If participants have any questions, they will be free to ask them. Then, being fully informed, they will be able to decide whether or not to participate in the study.

**3.7 Interventions**

**3.7.1 Explanation for the choice of comparators**

We intend to select the prevailing standard (nonstimulating) allopathic therapy as the control condition to determine if the expected benefits of cardiovascular ultrasound therapy will produce better anti-inflammatory results than standard therapy.

**3.7.2 Intervention description**

Participants allocated to the intervention group will undergo a 10-day regimen utilizing a medical cardiovascular ultrasound therapy device (838C-M-L-I/II, Shenzhen, China). The ultrasound instrument is equipped with a sound head comprising five transducer units operating at an ultrasonic frequency of 0.84 MHz with a sound intensity range of 1 W/cm^2^–1.25 W/cm^2^. The therapeutic ultrasound sessions require a controlled environmental temperature. Patients will assume the supine position, exposing the precordial region, with the 5-pronged head positioned parallel to the heart’s long axis; it should cover the entire precordial region including the right and left coronary arterial trunks and the aortic root (Fig.1). The five transducer units function sequentially in a scanning pattern, with each unit operating for 5 seconds and transitioning with a 0.5-second interval, following a clockwise rotation until the treatment has been completed. The cardiovascular ultrasound therapy device operates in a pulsed mode, and each treatment session lasts for 20 minutes; there would be two daily sessions for a total of 20 treatments. The control group was not given extracorporeal cardiac ultrasound therapy. Participants in the control group will not receive cardiovascular ultrasound therapy. cardiovascular ultrasound therapy will be assessed at baseline (24th-hour post-PCI), on the 10th day, and at the end of the first and third months post-intervention. If it is necessary to change the medication regimen as much as possible, if it is necessary to change the medication regimen, it should be decided after evaluation by the investigator, and if the medication regimen that does need to be changed has an impact on the test results, the patient should be excluded and the reasons for changing the medication regimen should be recorded in detail.

[figure not shown]

Fig. 1. Diagram of ultrasound head placement.

A: Patients undergoing cardiovascular ultrasound therapy. B is used in patients with occlusion of one coronary artery and C is used in patients with occlusion of both coronary arteries.

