**3.2.2 Exclusion Criteria:**

• ST-segment elevation myocardial infarction and non–ST-segment elevation myocardial infarction;

• Occlusion of branch vessels during PCI;

• Perioperative use of hormones or immunosuppressants;

• Combined infection or other inflammatory diseases;

• Postoperative fever;

• Allergy to contrast media or cardiovascular ultrasound acoustic head–related materials;

• Changes in lipid-lowering, antiplatelet, and antihypertensive drug regimens during treatment;

• A clear diagnosis of autoimmune disease;

• A history of other surgeries or trauma in the preceding 7 days;

• Infection with the novel coronavirus during the preceding month;

• Previous PCI treatment;

• Previous cardiovascular ultrasound treatment;

• Diabetes mellitus.

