**3.3 Criteria for the withdrawal of subjects from the trial**

**3.3.1 Subjects withdraw from the test on their own**

Patients can voluntarily withdraw from the trial at any time without providing any reason; or the subject has not explicitly withdrawn from the trial, but is no longer receiving LIPUS treatment or related indicators, it is also considered "withdrawal". Whenever possible, understand the reasons for the subject's withdrawal and document them in the case report form. Every effort should be made to keep the patient in the study and to continue with the required study-related treatments and markers.

For patients who voluntarily withdraw from the trial, the reason for withdrawal, the course of treatment, the time of the last treatment, and the results of the most recent test should be clearly recorded; The relationship between the branch or shedding in the trial and the trial should be carefully recorded, the possible impact of the discontinued case on the research conclusion should be analyzed, and the case report form should be completed and completed; Keep the original data of all exfoliated cases.

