**3.3.2 Withdrawal/drop-off as determined by the investigator**

The withdrawal decided by the investigator refers to the fact that the enrolled subjects are not suitable to continue the trial during the trial, and the investigator decides to withdraw from the trial.

1) During the trial, there are changes in the subject's condition, such as acute stent thrombosis, malignant arrhythmia, contrast nephropathy, acute left heart failure, hemodynamic instability, etc., which affect the compliance of continuing to participate in the trial or continue to participate in the trial may affect the safety of the subject, and the investigator believes that the patient should withdraw;

2) Patients with a definite diagnosis of PCI-related myocardial infarction at 48h;

3) Subjects who violate the inclusion/exclusion criteria, or have poor protocol compliance.

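### Intention-to-treat is promised, but the protocol excludes randomised patients after drug changes and lets criteria violations or undefined poor compliance end participation

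*Protocol*

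**What the plan says.** **Analysis principle.** Section 4, repeated in the statistical row of the Summary, states: "Analysis of both primary and secondary outcomes will be based on the intention-to-treat approach". It explains this as "ensuring that all participants remain assigned to their original group throughout the study". That speaks to group labels and does not say that every randomised patient is analysed.

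**Drug changes.** Section 3.7.2 says of a needed change that "it should be decided after evaluation by the investigator", and then: "if the medication regimen that does need to be changed has an impact on the test results, the patient should be excluded". Section 3.2.2 and the Summary's subject-population row list as an exclusion criterion: "Changes in lipid-lowering, antiplatelet, and antihypertensive drug regimens during treatment".

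**Withdrawal by the investigator.** Section 3.3.2 covers patients already enrolled. Its third item is "Subjects who violate the inclusion/exclusion criteria, or have poor protocol compliance". Its second item is "Patients with a definite diagnosis of PCI-related myocardial infarction at 48h", and its first covers clinical deterioration.

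**Withdrawal by the patient.** Section 3.3.1 also counts as withdrawn a patient who is "no longer receiving LIPUS treatment or related indicators". It asks for efforts to keep patients in the study and for existing data to be retained.

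**Masking.** Under section 3.5 attending physicians and patients know the allocation. Only those who collect primary outcome data are masked.

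**Missing data.** Section 4.3 plans comparisons across missing-data scenarios and multiple imputation when losses reach 10%.

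**The concern.** A drug change during treatment happens after allocation, so it cannot work as an entry criterion. Followed as written, it takes randomised patients out of the trial. The rule in section 3.7.2 goes further, because it ties exclusion to an effect on the results and gives no criterion for judging that effect. The results in question include hsCRP and IL-6, the primary outcomes.

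Intention-to-treat protects the comparison only if membership of the analysis does not depend on what happens after randomisation. Here it can depend on drug changes and on compliance. Both may differ by arm in an open-label trial, and both may be related to inflammation. If they are, the difference in hsCRP or IL-6 on day 10 no longer estimates the effect of allocation alone. The protocol also leaves two teams free to form different analysis sets from the same data, each with textual support.

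**Working it through.** **1. The passages side by side.**

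- Section 4 and the Summary: outcomes are analysed by intention-to-treat.
- Section 3.7.2: a patient whose drug change affects the results is excluded. This is exclusion wording, applied after allocation, and conflicts directly with section 4.
- Section 3.2.2 and the Summary: a change during treatment is an exclusion criterion. Through the third item of section 3.3.2, breaching a criterion becomes a reason for withdrawal, so any such drug change can end participation.
- Section 3.3.2, third item: inadequate compliance has the same consequence and is not defined.
- No section expressly provides that a withdrawn patient is still sampled on day 10 and analysed as randomised.
- No section requires the decisions in 3.3.2 or 3.7.2 to be made without knowledge of the arm.

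The contradiction rests on this text and not on the figures below.

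**2. The plan's own figures.** Section 3.4 gives 160 evaluable patients and 20% dropout: 160 / (1 − 0.20) = 200, as stated. It gives no SD, so the 160 cannot be checked. The SD that would produce it follows from 80 per group, a difference of 4 mg/L, two-sided α of 0.05 and 90% power:

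SD = 4 / [(1.960 + 1.282) × √(2/80)] = 4 / 0.5125 ≈ 7.80 mg/L (7.76 with the t-test).

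**3. Illustration of possible bias.** These assumptions are not from the documents: normal values, SD 7.8 mg/L, no true effect, 100 per arm, and patients with higher hsCRP more likely to be removed, with a set correlation between removal and outcome. Each cell has 4,000 simulated trials and shows the mean difference (ultrasound minus control, mg/L) and the two-sided t-test rejection rate. The Monte Carlo standard error is √(0.05 × 0.95 / 4000) ≈ 0.3 percentage points at a 5% rate.

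| Removed: ultrasound / control | Corr. 0 | Corr. 0.3 | Corr. 0.5 | Corr. 0.8 |
|---|---|---|---|---|
| 10% / 0% | 0.02; 4.6% | −0.44; 7.0% | −0.76; 10.4% | −1.20; 20.5% |
| 15% / 5% | 0.02; 5.7% | −0.37; 5.7% | −0.64; 9.5% | −1.02; 17.7% |
| 10% / 10% | 0.00; 5.1% | −0.01; 5.0% | 0.01; 6.0% | −0.02; 7.7% |

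Against the 4 mg/L target, the first row's spurious differences are 0.44/4 = 11%, 0.76/4 = 19% and 1.20/4 = 30%.

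**4. Worst case for ten removals.** If exactly the highest 10 of 100 values leave one arm, its mean shifts by φ(1.282)/0.90 × SD = 0.195 × 7.76 ≈ 1.5 mg/L, and simulated type I error is about 30%. Nothing in the documents suggests that removal would be this selective.

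**5. Reading.** Mean bias needs removal that is both related to outcome and unequal between arms. The rules permit this but do not make it certain.

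**The case against.** The strongest reply is that withdrawal is not removal from analysis. Sections 3.3.1 and 3.3.2 name no analysis set, and withdrawal can coexist with intention-to-treat through missing-data handling. Section 3.3.1 asks that treatments and markers continue where possible and that the effect of discontinued cases be examined. Section 4.3 plans extreme missing-data scenarios and, after a significant result, asks how strong an interaction between arm and missingness would overturn it. Neither step depends on the 10% threshold, which governs only imputation. All of this stands. A reader might infer that every withdrawal rule contradicts section 4, but the text does not support that. What remains is that section 3.7.2 says excluded, that section 4.3 addresses missing values and not deliberate exclusion, and that continued sampling after withdrawal is an aim and not a rule.

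Other stronger readings also go beyond the text:

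- **Only the ultrasound arm can be deemed withdrawn.** The treatment half of the definition in 3.3.1 is one-sided, but a control patient who stops assessments meets the other half.
- **The infarction rule strips the worst troponin and CK-MB cases.** The time of randomisation is not stated, although 48 h falls after the 24 h baseline and the rule concerns enrolled patients. These markers have no 48 h sample, the rule is the same in both arms, and the documents do not say that such patients would have the most extreme values at the scheduled visits.
- **Unmasked staff certainly decide.** Sections 3.3.2 and 3.7.2 name the investigator, while 3.5 unmasks attending physicians. That they are the same people is a fair inference but not a statement.
- **Exclusion depends on the observed outcome.** The sentence in 3.7.2 may instead mean a drug expected to influence the assays. The wording is ambiguous, which is itself a reason to replace it.

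**Conclusion.** The point holds. The intention-to-treat promise in section 4 and the Summary conflicts with the exclusion rule in section 3.7.2 and with the drug-change criterion in section 3.2.2 and the Summary, which section 3.3.2 turns into grounds for withdrawal. Undefined poor compliance adds a further discretionary route out. These rules can bias the hsCRP and IL-6 comparison; the documents do not show that they will, or in which direction.

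The size is illustrative only and rests on the back-solved SD of about 7.8 mg/L, normal data and no true effect. With 10% removed from one arm and correlation 0.3 to 0.8, type I error is about 7% to 21%. A reader might take the 30% figure as the expected inflation, but it is the extreme for ten removals from one arm. With equal or non-selective removal the mean bias is essentially nil.

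It should be settled before any patient is excluded, because it decides who enters the primary comparison and samples not taken cannot be recovered later.

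**What to change.** 1. **Section 3.2.2 and the Summary:** delete the item on drug changes during treatment, so that exclusion criteria rest on facts known before randomisation. Both places need the change, or the contradiction survives in the Summary.
2. **Section 3.7.2:** replace the exclusion sentence by recording the change, its reason and its date, with the patient staying in the primary analysis in the assigned arm.
3. **Section 3.3:** state that stopping study treatment or poor compliance does not end outcome sampling unless consent is withdrawn, and that all randomised patients are analysed as assigned.
4. **Sensitivity analysis:** if exclusions for drug changes or compliance are wanted, confine them to a per-protocol set with predefined criteria and with membership fixed blind to arm and results.
5. **Safety and infarction withdrawals in section 3.3.2:** these are clinical decisions and are not reworded here. They need only be reconciled with section 4 as to later follow-up and analysis.

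The cost is protocol wording, continued sampling of patients who would otherwise leave, and slight dilution of the effect by patients who change drugs or miss sessions.
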